### Inclusion and Exclusion Criteria

The criteria for inclusion are as follows: (1) femur fracture diagnosis, (2) 18 years of age or older, (3) knowledge of Spanish language, (4) 24-hour admission into the traumatology unit, (5) awareness level of 15 on a Glasgow scale, (6) access to mobile devices, (7) ability to participate in the pilot study, and (8) ability to provide written informed consent personally or to obtain consent via a legal representative. Criteria for exclusion are as follows: (1) presence of psychological pathologies or cognitive impairment and (2) treatment in isolation during hospitalization.

### Ethics Approval

This study has been approved by the Regional Health Research Ethics Committees of the Hospital Clínic de Barcelona (HCB/021/0341).

All questionnaires are confidential, and all patients must sign the informed consent according to the current Spanish legislation. In compliance with the current law on data protection and guarantee of digital rights, no data will be shared without express authorization, preserving patients’ confidentiality and anonymity of their identity at all times. Their participation will be voluntary, and their anonymity will always be preserved. This will be achieved by anonymizing the names or any personally identifiable information.

### Intervention

The final app is named MyPlan. it is based on a platform developed by the nonprofit organization Trilema, with the support of Amgen laboratory. The app is user-friendly and intuitive, and it allows patients to see their updated medication plan on their mobile phones at all times in a safe and private environment (Figure 1). One of its main functions is the daily (Figure 2) and monthly (Figure 3) calendar, and it also features reminders and allows adding programmed activities (eg, medication times, check-ups, and appointments). MyPlan is also a tool that supports treatment, allowing patients to plan and validate individual medication intake (Figure 4).

To ensure that the intervention works as expected and patients are able to access the app, the PI has a private area in MyPlan (Figure 5), where every individual patient is registered with a personal username and password. The PI will also add their individual medication plans so that patients are able to view them on the app.

The nursing pharmacological education intervention will be performed by a single nurse (an employee of Hospital Clínic de Barcelona) and the PI. This intervention consists of 4 sessions (Figure 6). First, the nurse will introduce themselves to the patient as the professional who will carry out the training session. Subsequently, patients will be informed about the intervention and its objectives. They will be introduced to MyPlan app, which will be downloaded on their smartphone, and a username and password will be generated for them (30 minutes). Then, the prescribed treatment and any questions from the patient about it will be discussed and reviewed (20 minutes). Finally, the session itself will be evaluated (10 minutes), using the Morisky-Green scale, as well as the PI’s review of the patient’s use of MyPlan during the admission, making sure they have pressed “OK” at the time they were taking the medication according to the prescription.

**Figure 1 figure1:**
[figure not shown]
MyPlan app; medication plan.

**Figure 2 figure2:**
[figure not shown]
MyPlan app; daily calendar.

**Figure 3 figure3:**
[figure not shown]
MyPlan app; monthly calendar.

**Figure 4 figure4:**
[figure not shown]
MyPlan app,; individual medication.

**Figure 5 figure5:**
[figure not shown]
MyPlan app; private area.

**Figure 6 figure6:**
[figure not shown]
The nursing pharmacological education intervention (EFE).

Positive mental health will be promoted in every session by giving patients the opportunity to explain how they are feeling, telling them that it is normal to feel sadness and frustration during hospitalization, but also encouraging them to think about the small daily achievements like decrease in pain or improvement in mobility. If the negative feelings persist, the patient will need to ask for help. The nurse will constantly encourage the patient to try to maintain a positive mindset and think that the final outcome will be good. The patient must value the positive things they have in life and cultivate interpersonal relationships. They will receive help in trying to find activities that will help them achieve a state of mental relaxation. This action will be evaluated by using the Positive Mental Health questionnaire.

The patient's experience will be measured with the Patient Experience Questionnaire-15. These tools have been added into MyPlan, making it agile to fill them out and export their data.

### Procedure

Following the inclusion and exclusion criteria defined in the study, the patient will be requested to answer the different questionnaires described in the “measurement tools” section.

The PI will download the MyPlan app for the patient and explain its function to them. The PI will also manually transcribe the treatment that has been prescribed for the patient’s hospitalization time. The medication that must be administered to the patient and the medication schedule will be added into the app. The PI will also carry out a basic training session for each medicine prescribed to the patient, including what the drugs are for and their possible adverse effects.

During hospitalization, the same procedure will be repeated every day from Monday to Friday. A minimum of 4 sessions, as described above, will be held to educate the patient and improve their knowledge in pharmacology and autonomy upon discharge. The PI will maintain an individual registry in a Microsoft Excel spreadsheet that will contain all adverse drug reactions notified in the patient’s clinical history. These data will be extracted from the information in the Systems Applications and Products in Data Processing bed chart (there is a shortcut icon for adverse drug reactions notifications), which is filled in by the medical professionals in charge of any given patient during hospitalization when applicable. As soon as the patient has been deemed fit to be discharged, the treatment prescribed for the time after discharge will be explained to them using the app (we will restrict the explanations to those pertaining to the treatment specified in the discharge report). It will be explained to them that they can use the app during the 30 days following discharge, as long as their primary care doctor does not make modifications to the treatment. For this reason, the patient’s history will be reviewed daily by the PI to make sure there have been no consultations that have resulted in a change in the medication; 25 days after discharge, the PI will contact the patient via the MyPlan app to ask them to fill out the questionnaires and remind them that the study will end 5 days later (ie, 30 days after discharge). A message will be sent to the patient via the app 30 days after discharge to thank them for participating in the study, and their access to the app will be blocked, considering that the intervention has concluded.

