### Participant Selection and Recruitment

Eligible participants will be identified in the hospitalization unit through the observation of a census by the principal investigator (PI) with a nonprobabilistic sample (according to the patients’ willingness to participate).

The sample calculation will be made by taking into account the total number of patients treated in the traumatology service for a femur fracture diagnosis during 2020. Approximately 494 patients are admitted annually with a femur fracture diagnosis. GRANMO software (version 7.12; IMIM Medical Informatics Unit) will be used with a 95% CI and a maximum indeterminacy of *P*=.5, accounting for a 15% loss, for a final recommended sample of 278 subjects to ensure a sufficient sample size for the analysis of the different variables.

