### Data Analyses

The statistical analysis will be made using Stata (version 15; StataCorp). It will consist of obtaining the differences between different data collections (24 hours after admission, upon discharge, and 25 days after discharge) for every variable considered in this project as a performance measurement of the intervention. Efficacy, effectiveness, and efficiency indicators will be based on the study of change from before the intervention to after the intervention (ie, before the intervention; upon discharge; and the last control, 25 days after discharge at home). These will be based on relative indexes (ie, change percentages) and reliable change indexes (ie, Jacobson-Truax coefficient as well as alternative indexes, such as Tsu, Hagerman-Arrindell, and Speer-Greenbaun indexes). The difference in quantitative measurements in different phases will be based on factorial analysis (ANOVA). These will provide the main effects of change for all different phases. They will also provide the reliability intervals of the averages and the differences of proportion as measures to be assessed, as well as that of standardized indexes, such as Cohen *d*.

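### The discharge instruction ties app use to unchanged treatment, while the day-25 questionnaires are requested through the same app: a minor, avoidable risk of informative loss at the last control

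*Protocol article*

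**What the plan says.** All references are to the Protocol article.

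- **Condition on app use (Procedure).** The explanation given at discharge is that patients "can use the app during the 30 days following discharge, as long as their primary care doctor does not make modifications to the treatment".
- **Monitoring (Procedure).** Because of that condition, the principal investigator (PI) reviews each history daily "to make sure there have been no consultations that have resulted in a change in the medication". The article states no step to follow when a change is found.
- **Day-25 request (Procedure).** Twenty-five days after discharge, "the PI will contact the patient via the MyPlan app to ask them to fill out the questionnaires". No exception is made for patients whose treatment has changed, and no other route is named.
- **Where the questionnaires sit (Intervention, text after Figure 6).** "These tools have been added into MyPlan, making it agile to fill them out and export their data".
- **End of access (Procedure).** The only block mentioned comes at day 30, when "their access to the app will be blocked, considering that the intervention has concluded".
- **Plan display (Intervention).** Of the app it is said that "it allows patients to see their updated medication plan on their mobile phones at all times". The PI enters the individual plans through a private area.
- **Role of day 25 (Data Analyses).** It is "the last control, 25 days after discharge at home", and the analysis rests on differences between the three data collections.
- **Allowance for loss (Participant Selection and Recruitment).** The calculation is described as "accounting for a 15% loss, for a final recommended sample of 278 subjects".

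**The concern.** The app has two roles after discharge. It shows the medication plan, and it carries the outcome request. The condition is sensible for the first role, because a patient should not follow a plan that primary care has replaced. As worded, however, it covers use of the app as a whole, and so reaches the second role too.

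A patient whose medication is changed on day 10, say, and who remembers the instruction has been given a reason to stop opening the app. The intervention then ends early for that patient, and the day-25 message may go unseen. Loss of this kind would not be haphazard. It would follow a consultation that altered the medication, which is plausibly related to adherence, one of the outcomes. A later analysis plan can choose how to handle missing values, but it cannot recover questionnaires that were never answered.

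**Working it through.** **1. The statements side by side.** App use is conditional on unchanged treatment. The day-25 request travels through the app. At least some of the questionnaires are completed in it. Day 25 is the last control. Each statement is explicit. Only the patient's reaction is inferred.

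**2. What a missed day 25 removes.** Three collections (24 hours after admission, discharge, day 25) give three pairwise differences. Without day 25, only admission to discharge remains, so the patient drops out of two of the three.

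**3. The plan's own figure.** The 15% allowance on 278 is 0.15 × 278 = 41.7 patients, which leaves 236.3. The 278 itself cannot be strictly reproduced, because the article gives no precision. With a finite population of 494, a proportion of 0.5 and 95% confidence, a precision of about 4.6% gives 236, and 236 / 0.85 = 277.6, that is 278. Nothing below depends on this.

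**4. Possible loss, under assumptions.** Let c be the share of app users with a treatment change by day 25, and f the share of those who then miss the questionnaires. The documents give neither. Both are assumed here: c from 10% to 30%, f from 25% to 100%. The loss is L = c × f.

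| c | f | L |
|---|---|---|
| 0.10 | 0.25 | 2.5% |
| 0.20 | 0.50 | 10% |
| 0.30 | 0.50 | 15% |
| 0.30 | 1.00 | 30% |

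L is a share of app users, whereas the 15% is an allowance on all 278, whose split between groups is not given. The two can be compared only loosely. The allowance may also already cover some of this loss.

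**5. Direction, as illustration only.** Let true day-25 adherence be 50%. The Introduction gives this as a general figure, and it is not specific to femur fracture. Let x be adherence among the lost patients (assumed, 30% to 70%). Observed adherence is (0.50 − L·x) / (1 − L).

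- L = 0.025: x = 0.30 gives (0.50 − 0.0075) / 0.975 = 50.5%, or +0.5 points. x = 0.70 gives −0.5.
- L = 0.15: x = 0.30 gives (0.50 − 0.045) / 0.85 = 53.5%, or +3.5 points. x = 0.70 gives −3.5.
- L = 0.30: x = 0.30 gives (0.50 − 0.09) / 0.70 = 58.6%, or +8.6 points. x = 0.70 gives −8.6.
- x = 0.50 gives no bias at any L.

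The sign depends wholly on x, and the largest values need 30% changed with every one of them lost. These figures show that the documents do not settle size or direction. They are not estimates.

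**The case against.** The best defence is that the harm is not in the text. On the natural reading, the condition is a medication-safety caveat: the plan on the screen holds only while the discharge prescription stands. The article never links it to the questionnaires. A patient with a change still has the app, is still sent the day-25 message and can still answer it. Loss needs the patient both to read the caveat as an order to stop using the app and to overlook the message. The PI looks for changes daily and has the means to enter plans. Finally, the action after a change and any fallback contact are details that an article leaves to the full protocol.

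Most of this stands. A reader might infer that patients with a changed treatment are locked out or withdrawn, or that their day-25 data are certain to be missing. The documents do not support that: the only stated block is at day 30, and the day-25 contact has no exception. A reader might also infer that all three questionnaires exist only in the app. The sentence on the tools follows the mention of the Positive Mental Health and Patient Experience questionnaires, so the place of the Morisky-Green is less certain, although the request for the questionnaires goes through the app in any case. Nor is any bias in the comparison with controls shown, because the article does not say how controls are measured at day 25.

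What remains is not a complaint about missing detail. The instruction is stated, patients are to be told it, and it works against the stated collection route. If plans can be updated after discharge, the condition is broader than it needs to be. If they cannot, the intervention stops early for these patients.

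**Conclusion.** The point holds as a minor one. A stated instruction gives patients with a changed treatment a reason to leave the channel through which the last control is requested. The resulting loss is possible, not certain. It would be tied to a clinical event and so may be informative.

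Neither its size nor its direction follows from the documents. The range of 2.5% to 30% of app users rests wholly on assumed rates, and the bias figures rest on further assumptions and include zero. The conclusion needs only one premise beyond the text: that some patients will take the condition literally.

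**What to change.** - Reword the discharge instruction so that a treatment change affects only the displayed medication plan, and tell patients to keep using the app for messages and questionnaires.
- When the daily review finds a change, have the PI update the plan or hide the outdated view. This keeps the safety purpose of the condition.
- State that the day-25 questionnaires are requested from every enrolled patient whatever happens to the treatment, with a telephone call if the app request is not answered.
- Record the date of any change and the response mode, and report how many patients had a change and how many of them answered. For patients already past day 25, this reporting is the part that can still be done.

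The cost is one or two sentences and a little PI time, since the PI already enters plans and reviews histories daily. The downside is a few telephone calls and a possible small difference between telephone and app answers, which is why the mode should be recorded.

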### Demographics and Baseline Functioning

Background data about the participants will be collected in the first session of the nursing pharmacological education intervention with the objective of evaluating any significant differences in the results after completion of the test. This background data will include age, gender, nationality, level of education, cohabitation status, caregiver, treatment, time of hospitalization, number of previous hospitalizations, evaluation of own health, and adverse effects.

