## Introduction

### Overview

The estimated amount of femur fractures by 2050 is 6 million worldwide. Due to the increase in life expectancy, the incidence of femur fractures in people older than 65 years is close to 4-6 cases per 1000 inhabitants per year in Spain, Catalonia, being the region with the highest incidence of femur fractures [1]. It has been shown that the population experiencing this type of fracture exhibits a high degree of complexity, causing an increase in morbidity, mortality, and subsequently, health care expenditure [2]. It is, therefore, necessary to establish an adequate health care quality, where the affectivity of the treatment and the safety of the patient are guaranteed [3].

There is evidence of the relationship between a good patient experience and both direct and indirect clinical results, which leads to better prognosis, faster discharges, and lesser use of medication [4,5]. Another important factor is the relationship between positive mental health and capacity for self-care. The more positive patients’ mental health is, the better their ability for self-care will be, and vice versa [5-7]. Another key factor, as the literature indicates, is health education for patients regarding their illness and its treatment. The more knowledge they have, the better their health and ability for self-care will be [8,9]. We usually find education studies focused on patients diagnosed with chronic diseases [10], but we rarely find studies that evaluate the effectiveness of education and information in relation to medication adherence.

When informing patients about medication, the term “10 rights” [11] regarding the safe administration of medication should also be mentioned—inform the patient about the medication that is being used, how it must be taken, what it is being used for, and what secondary effects or adverse reactions may derive from its use. The importance of this point stands out in two aspects: (1) the patient’s health education regarding all the medications they take, so they understand everything related to the care of their illness; and (2) the potential detection of errors on the patient’s part, acting as the last filter just before the administration of the drug by the nurse. This point is so important that not informing patients is considered a medication error in some studies [12].

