### Design

This protocol describes a nonrandomized, quasi-experimental study with a pretest-posttest control group.

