### Potential Limitations and Implications

The main limitation of this study is that the sample is not randomized. Another limitation presented is the selection of patients included in the study according to the level of awareness and cognitive capacity as well as the ability to understand and use the MyPlan app.

The training nurse’s time availability to train and educate patients in their pharmacological treatment is another limitation to take into consideration.

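### Nonrandomized study with a control group: the stated analysis has no group term or covariates, and the background form is tied to an intervention session and mixes in post-baseline variables

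*Protocol article*

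**What the plan says.** - **Design:** "This protocol describes a nonrandomized, quasi-experimental study with a pretest-posttest control group".
- **Participant Selection and Recruitment:** patients enter "with a nonprobabilistic sample (according to the patients’ willingness to participate"). No rule is given for who becomes a control.
- **Potential Limitations and Implications:** "The main limitation of this study is that the sample is not randomized". No analytic remedy follows.
- **Demographics and Baseline Functioning, timing:** "Background data about the participants will be collected in the first session of the nursing pharmacological education intervention".
- **Same section, purpose:** the data are taken "with the objective of evaluating any significant differences in the results after completion of the test".
- **Same section, content:** "This background data will include age, gender, nationality, level of education, cohabitation status, caregiver, treatment, time of hospitalization, number of previous hospitalizations", and then "evaluation of own health, and adverse effects".
- **Data Analyses:** differences between the three measurement times, percentage change, reliable change indexes, ANOVA over the phases giving main effects of change, intervals, and Cohen d. It names no group factor, covariate or propensity method.
- **Abstract (Methods):** sociodemographic data are a study variable, and the first measurement falls 24 hours after admission.
- **Procedure:** adverse drug reactions are extracted from a chart that the treating professionals fill in during hospitalization. The intervention is repeated every weekday of the stay.

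**The concern.** Patients are neither randomized nor sampled by a probability scheme, so the two groups may differ in age, education, home support, previous admissions and self-rated health. Each of these could plausibly affect adherence, experience or positive mental health, and how these change after a fracture. The article collects these variables but gives them no role in controlling for group differences. Its stated purpose is to look for differences in results afterwards, which is not adjustment.

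Two features of the form add to the problem. If it is completed literally in the first intervention session, controls would have no matching record, and an analysis plan written later could not create one. The form also counts length of stay and adverse effects as background. Neither is settled at a first session, and either may be affected by the intervention. An analyst who took the list as a ready-made adjustment set would be conditioning on possible consequences of treatment.

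**Working it through.** **Step 1: the passages side by side.**

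| Question | What the article states | Consequence |
|---|---|---|
| Is there a comparator? | Yes, a nonrandomized control group (Design) | A between-group effect needs confounding control |
| Does the stated model compare groups? | Only phases are named (Data Analyses) | The phase effect is not a group effect |
| Are covariates used? | Not in Data Analyses; elsewhere only to look for differences in results | No adjustment is stated |
| When is the form taken? | First intervention session (Demographics and Baseline Functioning), but a 24-hour measurement in the Abstract | The sections must be reconciled; controls have no such session |
| Are all items pre-intervention? | Time of hospitalization and adverse effects are included | Both accrue during the stay (Procedure) |

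**Step 2: how large the bias could be.** The point rests on no figure of the plan; 278 is used only to set an arm size. Assumptions not in the documents: a 1:1 split, and the imbalances and associations below.

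- Per arm: 278 / 2 = 139. After the stated 15% loss, 139 × 0.85 = 118.
- Continuous outcome: SE = √(2/118) = 0.130 SD.
- Bias = imbalance × correlation with the analysed outcome = 0.3 × 0.4 = 0.12 SD.
- Bias / SE = 0.12 / 0.130 = 0.92.
- Rejection under no effect = 1 − Φ(1.96 − 0.92) + Φ(−1.96 − 0.92) ≈ 0.15.
- With a correlation of 0.2 instead, bias = 0.06 SD, bias / SE = 0.46, and rejection is about 7.5%.

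For a binary outcome at 50%, SE = √(2 × 0.25/118) = 0.065:

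| Imbalance in a binary confounder | Its risk difference on the outcome | Bias | Rejection at nominal 5% |
|---|---|---|---|
| 10 points | 0.1 | 1 point | 5.3% |
| 20 points | 0.2 | 4 points | 9.4% |
| 30 points | 0.3 | 9 points | 28% |

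**Step 3: what change scores already do.** Subtracting baseline removes stable differences in level between groups. It does not remove confounding by a covariate that is related to change. If change is what is analysed, the correlation in Step 2 must be read as covariate with change, which may be below 0.4.

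**Step 4: precision.** With equal SDs and pre-post correlation r, the variance of a change score is 2(1 − r), and the variance after baseline adjustment is 1 − r².

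- r = 0.5: 1.00 against 0.75, a saving of 25%.
- r = 0.7: 0.60 against 0.51, a saving of 15%.

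**The case against.** The strongest reply is that this is a condensed article and the choice of covariates usually sits in the analysis plan, which is not shown. That would answer a complaint about missing detail. But the article does state a model and a use for the background data, and neither addresses confounding. The word factorial in Data Analyses might hint at a second factor, but phase is the only one named.

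Four stronger readings are tempting and are not supported:

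- **That background data are gathered only in the intervention session.** Measurement Tools lists forms for sociodemographic and clinical variables. Procedure asks for the questionnaires before it describes the app and training. The Abstract puts the first measurement at 24 hours. A collection point common to both groups may be intended, so the defect is a conflict between sections, not proof that controls lack data.
- **That the effect is confounded.** Size and direction cannot be known from the documents. Open to confounding is as far as they go.
- **That the plan adjusts for length of stay or adverse effects.** No section proposes it. The Overview does link good patient experience to a process "which leads to better prognosis, faster discharges, and lesser use of medication", but that is cited literature about experience, not a finding about this intervention. The risk lies in how the list is labelled.
- **That the 15% rejection rate describes this study.** It comes from assumed inputs, and the article gives no allocation ratio, power or effect size.

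It also stands that enrollment began in October 2022 and was due to finish in April 2023, the month the article was published. Re-timing the form is therefore largely no longer possible as a change of conduct.

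**Conclusion.** The point holds in a limited form. A nonrandomized study with a control group states an analysis with no group term and no covariates, so its between-group effect is open to confounding. Separately, the section on background data conflicts with the 24-hour measurement and labels two post-baseline variables as background.

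Under the stated assumptions, one moderately imbalanced covariate gives a bias of 0.12 SD and about 15% false rejection. Across the scenarios shown, rejection runs from 5.3% to 28%. These figures show plausible scale and are not estimates for this study. Baseline adjustment would also reduce variance by about 15% to 25% relative to change scores, for pre-post correlations of 0.7 to 0.5. This should be corrected, and the analysis part can still be corrected after enrollment has closed.

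**What to change.** 1. **State the contrast and adjust it.** Prespecify, before the outcome data are examined, a comparison of intervention with control at discharge and at 25 days. Adjust it for the baseline outcome score, age, gender, education, cohabitation or caregiver status, number of previous hospitalizations and self-rated health. Propensity weighting can serve as an optional sensitivity analysis.
2. **Reconcile the timing.** State that the background form belongs to the 24-hour assessment in both groups. For patients already enrolled without it, take what the records hold. Self-rated health is unlikely to be recoverable that way; if it is missing for one group, leave it out of the main model and say so.
3. **Relabel the post-baseline items.** Define time of hospitalization. Report length of stay and adverse effects as post-baseline variables, and state that they are not adjustment covariates.

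The cost is a revised analysis paragraph, one clarified sentence on timing and slightly more analysis work. No new variables are needed. Adjustment deals only with what was measured, so residual confounding should remain a stated limitation.
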